### Management of Confounding and Interaction Factors

The use of glucocorticoids for an indication other than treatment of an irAE will be considered a confounding factor. To control for this source of confounding, the dose and duration of glucocorticoid therapy will be minimised, and multivariate analysis will be adjusted for concomitant glucocorticoid use.

The coexistence of an autoimmune disease with cancer will be considered a potential effect modifier (i.e., interaction). Furthermore, female sex is known to be a risk factor for ANA positivity and high ANA titers (Li et al., 2011). To facilitate the interpretation of these two potential interactions, data will be presented for patient subgroups in the form of contingency tables.

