### Sample Size Calculation and Statistical Analysis

To estimate an expected sensitivity of the autoantibody panel under study of 0.90 with a 95% confidence interval of not less than 0.75, 70 cases with irAEs will be needed. Considering irAEs associated with ICIs will develop in 25% of cases (Wang et al., 2019), a total of 210 patients without irAEs will be required. Considering a loss to follow-up of 5%, we should recruit a total of 294 patients.

Regarding the statistical analysis, firstly, a description of the cohort will be performed. Quantitative variables will be reported as mean ± standard deviation or median (interquartile range) and compared between groups using Student’s t-test for unpaired data or the Mann-Whitney U-test, depending on whether data follow a normal distribution. Categorical variables will be expressed as frequencies (percentages) and compared between groups using Pearson’s Χ^2^ or Fisher’s exact test based on the expected frequency of cells. To assess the primary endpoint of the study (i.e., proportion of patients developing at least an irAE), the autoantibody panel will be considered positive when any of the autoantibodies included in the panel is positive according to the following cut-off points: ANA titers ≥ 1:40, ANCA titers ≥ 1:20 or RF value ≥ 30 IU/ml. The autoantibody panel and the titers of autoantibodies will be handled as a categorical variable (namely, positive or negative result) and as a quantitative variable, respectively. It is planned to perform a subgroup analysis depending on whether or not patients have an AD before their inclusion. An analysis of variance for repeated measures will be performed to explore the profile of detectable autoantibodies over the 48 weeks of follow-up.

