Survival will be assessed using a Kaplan-Meier analysis and compared between groups using the log-rank Mantel-Cox test. A subgroup analysis according to tumour type and extent of cancer (local, advanced, and metastatic disease) will be performed to assess survival outcomes*.* A multivariate analysis using logistic regression and Cox regression will be performed to detect factors associated with the occurrence of irAEs. Applying a manual backward stepwise procedure, a multivariate model will be constructed from variables that either have a p-value of less than 0.10 in the univariate analysis or are considered relevant to the dependent variable on the basis of previous studies (e.g., sex and age of patients, type of ICI). Variables not reaching statistical significance will be dropped from the final predictive model. The sensitivity, specificity, positive predictive value, negative predictive value, and probability ratios with their corresponding 95% confidence intervals of the model will be calculated. The diagnostic accuracy of the predictive model inferred from the logistic regression model will be described with the area under the receiver operating characteristic curve.

Two-sided hypothesis tests will be performed, and the significance level will be set at 5%. The statistical analysis will be conducted using IBM SPSS Statistics software version 27.0 (Chicago, IL).

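### The predictive model is selected by p-value from about 50 candidates with about 70 irAE cases and its accuracy is calculated in the same cohort, so the reported figures will be optimistic

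*Protocol article*

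**What the plan says.** All references are to the protocol article.

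- **Model building** (Sample Size Calculation and Statistical Analysis). A manual backward stepwise procedure starts from "variables that either have a p-value of less than 0.10 in the univariate analysis" or from variables supported by earlier work, with sex, age and type of ICI as examples. Then: "Variables not reaching statistical significance will be dropped from the final predictive model". Tests are two-sided at 5%.
- **Performance** (same section). Sensitivity, specificity, predictive values and likelihood ratios of the model are calculated with 95% confidence intervals, and "The diagnostic accuracy of the predictive model inferred from the logistic regression model will be described with the area under the receiver operating characteristic curve". No bootstrap, cross-validation, split sample, shrinkage or penalisation is mentioned.
- **Candidates** (Variables). A long list of clinical, tumour, treatment and laboratory items is to be collected and analysed as possible predictors.
- **Size** (Sample Size Calculation and Statistical Analysis). "70 cases with irAEs will be needed", and "a total of 210 patients without irAEs will be required". The stated purpose is "To estimate an expected sensitivity of the autoantibody panel under study of 0.90 with a 95% confidence interval of not less than 0.75", so the study is sized for the panel and not for developing a model.
- **Role** (Objectives). The diagnostic properties of a predictive model are a primary objective. The Secondary Objectives section closes by announcing external validation in an independent cohort as a later phase.
- **Adjustment** (Management of Confounding and Interaction Factors). Glucocorticoids given for reasons other than an irAE are named as a confounder, and the multivariate analysis is to adjust for them.

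**The concern.** When many candidates compete for few events, a p-value screen followed by backward elimination keeps some variables because they happen to fit this sample. Accuracy measured in that sample then credits the model with the chance fit. The AUC comes out too high, and the confidence intervals are too narrow because they treat the selected variables as if they had been fixed beforehand.

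The model's diagnostic properties are a primary objective, so the bias falls on a headline result. A model carrying noise variables would also be the one handed on to the validation phase.

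**Working it through.** **1. The plan's own figure.** With exact binomial limits and true sensitivity 0.90, 70 is the smallest number of cases at which the lower limit reaches 0.75 with 95% assurance (one-sided 95% limit), or with 90% assurance (two-sided 95% limit). Non-cases: 70 × 0.75/0.25 = 210. Total 280, and 280 × 1.05 = 294. The size reproduces, as a size for the panel's sensitivity.

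**2. Events per candidate.** My count from the Variables section, leaving out outcome items:

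- demographic and clinical 18
- tumour 3
- prior treatment 4
- ICI 4
- routine laboratory 19
- vitamin D 1
- autoantibodies 3, plus the panel 1

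The total is 53. Coding categorical items or using repeat samples would raise it. 70/53 = 1.3; with a round 50, 70/50 = 1.4.

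**3. What 70 events can support.** The shrinkage criterion for prediction models is n = p / [(S − 1) × ln(1 − R²cs/S)], with target S = 0.9. At 25% events the maximum R²cs is 0.675, so R²cs = 0.675 × Nagelkerke R². The Nagelkerke values are assumptions.

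| Parameters | Events needed, R² 0.15 | R² 0.30 | R² 0.50 |
|---|---|---|---|
| 50 | 1,047 | 491 | 266 |
| 10 | 210 | 99 | 54 |
| 7 (0.7 × row above) | 147 | 69 | 38 |

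Fitting 50 parameters without selection at n = 280 gives expected shrinkage of about 0.40, 0.58 and 0.72.

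**4. Simulating the stated procedure.** n = 280, 25% events, screen at p < 0.10 with three variables entered regardless, backward elimination at 0.05, and the model then tested in new patients from the same population. The no-signal and moderate rows use 300 replicates, with ranges covering assumed predictor correlations of 0 and 0.3 (the 10-candidate row uses 0). The planned-panel case with 50 candidates was run twice. Effect sizes and false-positive rates (FPR) are assumptions.

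| Signal | Candidates | Apparent AUC | AUC in new patients | Optimism |
|---|---|---|---|---|
| None | 50 | 0.62–0.64 | 0.50 | 0.12–0.14 |
| Moderate | 50 | 0.66–0.71 | 0.59–0.61 | 0.07–0.11 |
| Moderate | 10 | 0.66 | 0.63 | 0.04 |
| Panel sensitivity 0.90, FPR 0.30 | 50 | 0.84–0.85 | 0.80 | 0.04–0.05 |
| Panel sensitivity 0.90, FPR 0.30 | 20 | 0.82 | 0.80 | 0.02 |
| Panel sensitivity 0.90, FPR 0.50 | 50 | – | – | 0.07 |

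As a check, a single binary test with sensitivity 0.90 and specificity 0.70 has AUC (0.90 + 0.70)/2 = 0.80.

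**5. Sensitivity and specificity.** The article does not say how the model's cut-off is chosen. If it were the Youden point in the same data (an assumption), sensitivity/specificity would fall from 0.67/0.69 to 0.53/0.62 with moderate signal and uncorrelated predictors. With the planned panel (FPR 0.30, 50 candidates) it would fall from 0.88/0.73 to 0.83/0.72.

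**6. Glucocorticoids.** One section commits the multivariate analysis to adjusting for them. The statistical section describes one multivariate model and drops whatever is not significant, with no exemption. Both can be honoured only if glucocorticoid use happens to be significant.

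**The case against.** **Internal validation may be planned elsewhere.** This is a condensed article, and a bootstrap could sit in an analysis plan that is not shown. A reader might infer that the study has decided against any optimism correction. The article does not say that; it is silent. The selection rule and the calculation of accuracy are stated, however, and followed as written they give optimistic figures.

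**External validation is announced.** This stands and lowers the severity: the development AUC is not the project's last word. It does not correct the AUC, sensitivity or intervals that this study will publish.

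**The signal may be strong.** The pilot described in the Discussion found panel positivity of 87.5% against 30%, an odds ratio of (0.875/0.125)/(0.30/0.70) = 16.3. With a panel that strong the bias is at the low end. The pilot had 69 patients from one centre and may itself be optimistic, so the weaker scenarios cannot be ruled out. If irAEs were as frequent as in the pilot (37.5%), 280 patients would give 105 events and 105/53 = 2.0 per candidate, still very few.

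**The rule might look self-contradictory**, since sex, age and ICI type can enter on prior evidence and leave on a p-value. That reading fails: entry and retention are successive stages of one procedure. Nor does the remark that "female sex is known to be a risk factor for ANA positivity and high ANA titers" oblige a prediction model to keep sex. That is a confounding argument, and the same section already plans contingency tables by subgroup.

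**Conclusion.** The concern holds for the fitted model. Selection on significance from about 50 candidates with about 70 events, assessed in the same cohort, will overstate accuracy on a primary objective, and the confidence intervals will ignore the selection. The AUC optimism is about 0.02 to 0.07 if the panel reaches the planned sensitivity of 0.90 (assumed false-positive rate 0.30 to 0.50, 20 to 50 noise candidates), about 0.10 with a moderate panel and about 0.14 with no signal. The true signal is unknown, so the range is the honest statement.

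Two stronger readings are not supported. The first is that the panel's estimated sensitivity is biased: its cut-offs are prespecified, nothing about it is selected from the data, and its sample size reproduces. The second is that the model's sensitivity will be overstated by some definite amount: any such figure depends on a cut-off rule that the article does not give.

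The literal conflict over glucocorticoid adjustment also stands. Overall this should be fixed before analysis; it does not invalidate the study.

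**What to change.** **Needed.** Report optimism-corrected AUC, calibration slope, sensitivity and specificity from a bootstrap that repeats every modelling step: univariate screen, backward elimination and any cut-off chosen from the data. A smaller candidate pool does not remove the need, since 10 candidates still gave optimism of 0.04.

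**Preferable.** Prespecify a short core model kept regardless of p-value: panel, age, sex, ICI type, prior autoimmune disease and glucocorticoid use. With ICI type coded as three classes this is 1 + 1 + 1 + 2 + 1 + 1 = 7 parameters, or 70/7 = 10 events each; a term for combination therapy makes 8. Use penalisation, because seven parameters may need 147 events if the assumed R² is 0.15. Label screening of the remaining variables exploratory. Keeping glucocorticoid use in the core also reconciles the two sections.

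**Cost.** No new patients, samples or visits. The panel is not assayed until the whole cohort reaches week 48, so the model can be fixed before the main predictor is known. It takes some programming beyond the standard SPSS menus, and the headline AUC will be lower.

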## Methods and Analysis

### Objectives

#### Primary Objectives

• To identify predictive factors of irAEs at week 48 after the initiation of ICI therapy• To evaluate the diagnostic properties (sensitivity, specificity, positive predictive value, negative predictive value, likelihood ratios) of a predictive model of irAEs.

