Data related to the tumour:• Tumour type• Date of diagnosis• PD-L1 expression in tumour cells (%)• Date of initiation of ICI therapy• Dates of ICI administration• Date of progression• Date of death• Progression-free survival, defined as time from start of ICI therapy to tumor progression, death or last day of follow-up• Overall survival, defined as time from start of ICI therapy to death or the last day of follow-up• Cause of death: cancer-related, non-cancer-related, ICI-associated toxicity (immune-related, non-immune-related adverse event, infection or other).

Data related to treatment received before ICI initiation:• Nonsteroidal anti-inflammatory drugs• Glucocorticoids• Other immunomodulatory drugs: e.g., colchicine, hydroxychloroquine, mesalazine, or sulfasalazine• Oral anticoagulants (acenocoumarol, low-molecular-weight heparin, direct oral anticoagulants).

Data related to ICI:• Type: anti-CTLA4 (ipilimumab), anti-PD1 (nivolumab and pembrolizumab), anti-PD-L1 (atezolizumab, avelumab, and durvalumab)• Monotherapy or combination therapy (description)• Adjuvant or palliative therapy, and if palliative, line of therapy (first line, second line, other).

Laboratory data:

Obtained from blood samples for care and research purposes:• Glomerular filtration rate (ml/min/m^2^), levels of glucose (mg/dl), bilirubin (mg/dl), alanine aminotransferase, aspartate aminotransferase, gamma-glutamyltransferase (U/L), and thyroid stimulating hormone (μUI/mL).• Prothrombin time (percentage) or international normalized ratio (INR)• Complete cell count: haemoglobin (g/dl), white blood cells (/µL), differential white blood cell count of neutrophils, lymphocytes, monocytes, and eosinophils (/μL) and platelets (/μL)• Lipid profile: levels of cholesterol, triglycerides, and high- and low-density lipoprotein cholesterol (mg/dl).

Obtained from blood samples only for research purposes:• 25-hydroxycholecalciferol (ng/ml) at weeks 0, 24 and 48.• Levels of the autoantibodies under study (i.e., ANAs, RF and ANCAs) in ordinary samples according to study schedules (Figures 1, 2) and extraordinary samples.

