## Discussion

The progressive adoption of immunotherapy in various types of cancer and the growing trend towards the use of combinations of ICIs are extending the problem of irAEs to a larger number of patients (Ramos-Casals et al., 2020). A better understanding of the pathophysiology of irAEs would allow us to select more efficient clinical, analytical, and histological markers for the early and accurate detection of immune-mediated toxicity (Patil et al., 2018). To date, several immunological mechanisms have been proposed to explain the development of irAEs in cancer patients treated with ICIs: direct molecular mimicry, abnormal cytokine production, the influence of environmental factors such as the gut microbiome, activation of cytotoxic T cells, and activation of autoreactive B cells with secondary production of autoantibodies (Lee et al., 2021). The actual mechanism by which ICIs lead to autoantibody release has yet to be established. ICI-enhanced T-cell damage to tumour tissue could overexpress antigens that trigger B-cell activation (Thibult et al., 2013; Das et al., 2018). Alternatively, ICI-induced cytokines could indirectly activate B cells or their expansion into plasmablasts (Vazquez et al., 2015). In recent years, the potential use of autoantibody batteries as predictors of irAEs has become a promising and widespread field of research (Salim et al., 2021; Seki et al., 2021).

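### The study aims to evaluate the autoantibody panel, but the planned AUC belongs to a stepwise model that may also contain age, sex and type of ICI, with no comparison to a model without the panel

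*Protocol article*

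**What the plan says.** - **Aim.** The Abstract and the Summary of the Introduction both present the study as an evaluation of the panel (ANA, RF, ANCA) for identifying patients at risk of irAEs.
- **Primary objective.** The Primary Objectives section puts the accuracy measures on a model instead: "To evaluate the diagnostic properties (sensitivity, specificity, positive predictive value, negative predictive value, likelihood ratios) of a predictive model of irAEs".
- **Sample size.** This is set on the panel: "To estimate an expected sensitivity of the autoantibody panel under study of 0.90 with a 95% confidence interval of not less than 0.75", for which "70 cases with irAEs will be needed". One overall rate is used: "Considering irAEs associated with ICIs will develop in 25% of cases".
- **Model building.** Sample Size Calculation and Statistical Analysis describes manual backward selection. Candidates enter with a univariate p-value below 0.10 or because earlier studies make them relevant ("e.g., sex and age of patients, type of ICI"). Non-significant terms are then dropped. Sensitivity, specificity, predictive values and likelihood ratios are calculated for that model, and: "The diagnostic accuracy of the predictive model inferred from the logistic regression model will be described with the area under" the ROC curve.
- **Regimen.** Single agents and combinations enter one cohort (Participants). The Variables section records type of ICI by drug target and, as a separate item, "Monotherapy or combination therapy (description".
- **Subgroups.** Those named are prior autoimmune disease, tumour type and extent (for survival), and contingency tables by autoimmune disease and sex. Regimen is not among them.

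**The concern.** Three parts of the article point at different objects. The aim and the sample size concern the panel. The accuracy measures concern a selected model in which the panel is one of several candidates. An AUC for that model mixes the panel's contribution with that of age, sex and treatment, all of which are known before any autoantibody is measured. The question that would justify testing is how much better the prediction becomes once the panel is added, and a single AUC cannot answer it.

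This matters beyond the first report. The Secondary Objectives section says the model goes on to external validation in an independent cohort. If the comparator is not fixed beforehand, a model whose discrimination comes mainly from clinical variables could go forward as evidence for the panel.

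Regimen is a plausible contributor. The article names type of ICI as relevant to irAEs, and the Discussion says that "the growing trend towards the use of combinations of ICIs are extending the problem of irAEs to a larger number of patients". If irAE rates do differ by regimen, predictive values pooled over regimens will also differ from those within each.

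**Working it through.** **1. The plan's own figure.** 70 cases / 0.25 = 280 patients, of whom 210 have no irAE. 280 × 1.05 = 294, as stated (280 / 0.95 gives 295). The 70 cases also reproduce: 70 is the smallest number for which the exact one-sided 95% lower limit reaches 0.75 with probability at least 0.95 at a true sensitivity of 0.90 (probability 0.956). The sizing is thus coherent, and its target is the panel's sensitivity.

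**2. What regimen alone could contribute.** The documents give neither the share on combination ICI nor an irAE rate by regimen. Assumed: overall rate 25%, combination share f of 10% to 30%, combination irAE rate p of 40% to 60%. For a two-level marker:

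AUC = 0.5 + 0.5 × (f·p/0.25 − f·(1−p)/0.75)

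| f | p | Implied monotherapy rate | Odds ratio | AUC |
|---|---|---|---|---|
| 10% | 40% | 23.3% | 2.2 | 0.54 |
| 20% | 50% | 18.75% | 4.33 | 0.63 |
| 30% | 50% | 14.3% | 6.0 | 0.70 |
| 30% | 60% | 10% | 13.5 | 0.78 |

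Central case: f·p/0.25 = 0.10/0.25 = 0.40; f·(1−p)/0.75 = 0.10/0.75 = 0.133; AUC = 0.5 + 0.5 × 0.267 = 0.633. Of the nine combinations of f = 10, 20, 30% and p = 40, 50, 60%, seven fall below 0.70.

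**3. What regimen, age and sex could contribute together, without the panel.** Simulated logistic model, overall rate 25%. Assumed: 40% women, odds ratio for women 1.5 to 2.0, odds ratio for age 1.3 to 1.5 per standard deviation. With a 20% combination share and a regimen odds ratio of 4.33, the AUC is 0.68 to 0.71. Over shares of 10% to 30% and regimen odds ratios of 2 to 8, it is 0.61 to 0.78.

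**4. Comparison with the pilot.** The Discussion reports panel positivity of 87.5% with irAEs and 30% without. As a single yes/no test this is an AUC of 0.5 × (1 + 0.875 − 0.30) = 0.79. The pilot model with sex, age and panel had 0.906. If both figures describe the same patients, which the article does not say, the model's AUC exceeds the panel's by about 0.12. The two quantities are not interchangeable.

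**5. Predictive values if rates differ.** Take a panel-only test with sensitivity 0.90 (planning value) and specificity 0.70 (from the pilot's 30%), held constant across regimens, and apply Bayes' theorem:

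| irAE rate | PPV | NPV |
|---|---|---|
| 25% (pooled) | 0.225/(0.225+0.225) = 0.50 | 0.525/(0.525+0.025) = 0.955 |
| 18.75% | 0.169/(0.169+0.244) = 0.41 | 0.569/(0.569+0.019) = 0.968 |
| 50% | 0.45/(0.45+0.15) = 0.75 | 0.35/(0.35+0.05) = 0.875 |

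This shows the direction of the effect only. The planned measures belong to a model, and one that contains regimen would have sensitivity and specificity that vary by regimen at any single risk cut-off.

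**The case against.** **The selection procedure already tests the panel.** It is examined alongside type of ICI, and a panel with no independent effect would generally be dropped, visibly. This stands, and it protects the association: an adjusted odds ratio largely serves the purpose of a likelihood-ratio test. It does not measure added discrimination. A panel can be significant and still move the AUC very little.

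**Regimen alone would produce a good AUC.** A reader might infer this, but the figures do not support it. The central case gives 0.63. The value of 0.78 needs a monotherapy irAE rate of 10% and an odds ratio of 13.5. The only single-drug rate in the article, 37.5% in the nivolumab pilot of 69 patients, lies well above every monotherapy rate assumed here.

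**Pooled predictive values fit neither regimen.** A reader might infer this too. It needs regimen-specific irAE rates, which the article does not give, and the illustration above uses a fixed panel-only test rather than the planned model. If few patients receive combinations, the pooled values will lie close to those for monotherapy.

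**Results by regimen should be primary.** This would undercut the 70-case basis. With 280 evaluable patients, a 20% share and a 50% rate leave 280 × 0.20 × 0.50 = 28 cases. An observed 25/28 has an exact lower limit of 0.72, below the 0.75 target. The objection stands, so regimen-specific results should be secondary.

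**The article is condensed.** Silence on regimen does not exclude such an analysis, and the detail may be in a document not shown. That is fair for the subgroup question. The core point rests on what the article does state: the aim, the model-building rule and the object of the accuracy measures. Likewise, it should not be inferred that the panel's own sensitivity will go unreported. The sample size and the stated positivity rule suggest that it will be, but a stand-alone sensitivity does not show added value either.

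**Conclusion.** The concern holds in a limited form. The stated AUC and accuracy measures describe a selected model, the aim concerns the panel, and no comparison named in the article connects the two. As planned, the AUC cannot show how much the panel adds.

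Under the assumptions in step 3, an AUC of about 0.70 is compatible with a panel that contributes nothing, because regimen, age and sex can together reach 0.68 to 0.71. All the regimen, age and sex effects are assumed, so these values show what is possible and do not predict the result. The case for reporting by regimen is weaker and conditional: irAE rates may differ, but the documents offer no comparison. The sample size is not in question. The change is worth making before the data are analysed and the model goes to external validation.

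**What to change.** In Sample Size Calculation and Statistical Analysis:

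1. Fix in advance a reference model with age, sex and monotherapy versus combination ICI, exempt from stepwise selection. Fit it, and the same model plus the baseline panel result, in the same patients. Report the likelihood-ratio test and the AUC difference with its 95% CI.
2. Keep the pooled accuracy measures as the main result. Report sensitivity, specificity, predictive values, likelihood ratios and AUC for monotherapy and combination ICI as secondary and descriptive.

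Age, sex, regimen and baseline autoantibodies are already collected, so no new data or patients are needed. The cost is slightly more analysis and wide intervals in the smaller combination group, which the text should acknowledge.
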